### 5.3 Exclusion criteria

A potential subject who meets any of the following criteria will be excluded from participation in this study:

- Contraindication to CR
- Mental impairment leading to inability to cooperate
- Severe impaired ability to exercise
- Signs of severe cardiac ischemia and/or a positive exercise testing on severe cardiac ischemia
- Insufficient knowledge of the native language
- No access, availability or insufficient knowledge of a computer with internet
- Implanted cardiac device (pacemaker, ICD)

#### 5.4 Sample size calculation

In order to assess the effects on sustained physical fitness after participation in the *mCR* programme it was determined that an inclusion of 119 patients per group would be sufficient to examine the aim of this study.

This is based on the expected difference in increase in  $VO_{2peak}$  level of 3.0 ml/kg/min at 6 months between the control and intervention group with an estimated standard deviation of 5 ml/kg/min in the intervention group and 6 ml/kg/min in the control group. Assuming 80% power and 5% two-sided significance level ( $\alpha=0.05$ ), the sample size ( $n$ ) required to achieve a probability of 80% of detecting a difference in an increase  $VO_{2peak}$  level between two independent groups is  $n=55$  per randomisation group. Since patients from different centres (countries) will be pooled in the analysis, we will apply an adjustment for dependency of the observations to calculate the sample size, based on an estimated intraclass correlation coefficient (ICC) for the study centres.

The ICC is the proportion of the total variance which is between the centers rather than within centres. An ICC of 0.05 is used in the sample size calculations. After adjustment for the ICC the sample size is  $N=83$  per group. Based on 30% withdrawal we aim for a group size of  $n=119$  per randomisation group ( $n=238$  in total). Six centres will participate in the RCT so we will aim at including approximately 40 patients per centre. As this is a cooperative trial, centres may recruit more patients than this recruitment goal. When one centre starts to dominate enrolment however, recruitment might need to be capped. The total sample size ( $n=238$ ) would be sufficient to detect a clinically and physiologically relevant change in peak oxygen consumption, despite a 30% dropout.

## 6. TREATMENT OF SUBJECTS

### 6.1 Investigational product/treatment

Patients participating in the *mCR* programme (or intervention group) will undergo 6 months of mobile telemonitoring guidance and in addition another 6 months without mobile telemonitoring. The *mCR* group receives a heart rate monitor and smartphone with a special application to use for their training in their home environment. This smartphone can only be used by the patient for research purposes and will be given back to the researcher once the patient finishes the first 6 months in the study with mobile telemonitoring guidance. Instructions are given to the patient by the researcher, nurse or physician before they start training with a heart rate monitor and smartphone at home. Patients are instructed to exercise while wearing the heart rate monitor at 5 days per week for at least half an hour at an individual selected level of intensity and self-chosen type of activity. The outcomes of the maximal exercise tests on the first visit will enable to personalise the heart rate zones per patient in order to see (after every training/activity) in what zone the patient is training. At the moment patients start an exercise, they need to wear the heart rate monitor, and select on their smartphone the type of activity they are going to perform. While finishing the exercise patients have to register at the smartphone they are done and fill in the rate of perceived exertion (BORG-score). Accordingly, the duration, intensity (based on the heart rate zones) and BORG-score of each training/activity is collected by the smartphone and transferred to a secured website where both patient and researchers/nurses involved in the study can view the results. During the first month patients receive weekly individual coaching and feedback on their training results by telephone, in the second month this will be once per two weeks, whereas one monthly call will be held in the last four months (month 3 until 6) of the mobile telemonitoring period. Mobile telemonitoring guidance will help to improve the self-management skills and stimulate a patient to exercise independently. Besides the coaching by telephone and the advice to train 5 days a week for a minimum of 30 minutes at the start of the first 6 months, there will be no other advices given by the researcher, nurse or physician via the smartphone or secured website. At the end of the first 6 months, the patients are asked to return the heart rate monitor and smartphone to the researcher. In the second period without mobile telemonitoring (month 7 until 12) patients will receive no coaching or feedback by phone. Cardiac patients that are randomised to the control group will undergo 6 months with no *mCR* programme with another 6 months of follow-up in addition. During the study period both groups will receive standard outpatient care and control by a cardiologist. See paragraph 6.2 for more information about the way data are collected by the smartphone in the intervention group.

## **6.2 Data collection by smartphone**

Patients in the intervention group receive a heart rate belt and smartphone with a self-tracking application of MobiHealth which is able to measure physical activities. With this application patients can register the duration and type of activity they are about to perform from a predefined list (i.e. cycling, walking, et cetera) and subjective perceived exertion (BORG score) afterwards. The wireless connected heart rate belt measures the heart rate of the patient during the activity which will subsequently be transferred to the smartphone application by Bluetooth. Both patient and researchers/nurses/physicians involved in the study have access to a MobiHealth Rehabilitation™ portal where data is presented with regards to their personal guidelines set for activities. A personal guideline regarding the intensity and frequency for the self-chosen activity for the patient is entered once at the start of the study by the researcher/nurse/physician. MobiHealth has a CE marking for its software.

## 7. METHODS

### 7.1 Study endpoints/outcomes and baseline characteristics

[figure not shown]

## 7.2 Study endpoints/outcomes

### 7.2.1 Patient related study endpoints/outcome

#### Main study endpoint

- Difference in  $VO_{2peak}$  from an incremental exercise test (T1-T0)

#### Secondary study endpoints/outcome

- Difference in  $VO_{2peak}$  from an incremental exercise test (T2-T0, T2-T1)
- Traditional risk factors:
  - Changes in lipid profile (T1-T0, T2-T0, T2-T1)
  - Changes in HbA1C (T1-T0, T2-T0, T2-T1)
  - Changes in renal function (T1-T0, T2-T0, T2-T1)
  - Changes in lean body mass (T1-T0, T2-T0, T2-T1)
  - Changes in blood pressure (T1-T0, T2-T0, T2-T1)
  - Changes in smoking habit (T2-T0)
- MACE: the occurrence of events (cardiovascular (CV) mortality, all-cause mortality, near sudden cardiac death, ACS, CV intervention/surgery, CV hospital admission, CV emergency visits) as composite endpoint (T2-T0) are registered and collected by monthly telephone calls.
- General health:
  - Difference in depression score assessed by: PHQ-9 questionnaire (T1-T0, T2-T0, T2-T1)
  - Difference in anxiety score assessed by GAD-7 questionnaire (T1-T0, T2-T0, T2-T1)
  - Quality of Life: SF-36v2, difference in Physical Component Summary Score and Mental Component Summary Score (T1-T0, T2-T0, T2-T1)
  - Difference in dietary pattern (reflected by total score and score on individual components) assessed by Mediterranean Diet Score (T1-T0, T2-T0, T2-T1)
- Care utilisation as composite endpoint of: (number of) admissions, emergency visits and cardiac interventions (PCI, CABG) (T2-T0).
- Costs of care utilisation based on activities (clinical admission days, emergency and outpatient clinic visits, GP visits for cardiac (related) complaints or issues, radiology/cardiophysiology/nuclear and laboratory tests,

and cardiac interventions) registered at T0, T1 and T2 and collected by monthly telephone calls with the participants between T1 and T2.

### 7.2.2 Training related outcomes

- Adherence (number of drop-out or completed CR) throughout study period.
- Compliance: compliance to usage of the smartphone (percentage of fulfilling the planned exercise sessions with *mCR* for at least half an hour at 5 five days per week) in the intervention group is determined for the period between baseline and 6 months.

### 7.3 Patient characteristics

- Demographic data: gender, age, educational attainment, ethnicity, working
- Physical parameters weight, length, BMI, lean body mass
- Medical history:
  - Cardiovascular
  - Co-morbidity
  - Current complaints (angina, dyspnea)
- Risk factors
- Medication (T0, T1, T2)
- Indication for CR
- Exercise test parameters (T0, T1, T2)
- Echocardiographic parameters (LV function)

### 7.4 Centre characteristic

- Mobile telemonitoring guidance: the coaching by telephone is performed by a physician, nurse or researcher.

### 7.5 Randomisation, blinding and treatment allocation

At the start of the CR programme, once patients have indicated not to be interested in the regular CR programme, patients will be informed about the study and requested to participate. After receiving written consent from the patient they will be randomised in 1:1 ratio to the intervention group with mobile telemonitoring guidance or the control group with no mobile telemonitoring guidance or other CR programme by means of computerised allocation system applying an algorithm that prevents the care providers or the investigators from predicting the outcome of the randomisation

process. This means that the person, who determines if the patient is eligible, at the time of this decision, is unaware of which group the patient will be allocated to. The patient, care provider and outcome assessor will not be blinded to the intervention itself because of safety concerns.

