**Physical fitness**

Before the assessment of physical fitness, skinfold thickness will be determined (biceps, triceps, sub-scapular, supra-iliac) to calculate the lean body mass. (13)

Physical fitness level will be measured as the  $VO_{2peak}$  during an incremental maximal exercise test, using a continuous gas analyser. ECG and heart rate will be registered continuously and blood pressure will be measured at fixed intervals of 3 minutes. The test will be performed under supervision. The modality for the exercise test will be cycling. All tests will be performed by the same protocol. For patients who are not able to participate in a  $VO_{2peak}$  test, this test will be replaced by a 6 Minutes Walking Test. The testing modality chosen per centre at T0, will remain the same at T1 and T2. To ensure a safe environment in which the tests can be performed, the test will be performed to applicable guidelines and regulations within each participating centre.

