### **10.3 Benefits and risks assessment, group relatedness**

At all participating centres, there is a long-standing tradition in performing non-invasive testing as used in this present study. All procedures are performed routinely at the departments and have been accepted by the ethics committee in numerous previous applications in healthy as well as various patients groups.

Non-invasive cardiac testing procedures in this study are not related to any potential risk for the participant. Maximal ergometer tests will be performed at the hospital under supervision of highly qualified personnel.

A possible complication of venipuncture is a hematoma, which is induced in ~5% of all cases. To prevent complications, an experienced professional will perform the blood withdrawal and sufficient pressure will be provided after withdrawal of the needle. As patients are carefully instructed beforehand and individually coached by telephone on their physical progress during the first 6 months of the study we expect no potential risk for them to exercise in their home environment.

Taken together, our study involves minimally and non-invasive measures, whilst the *mCR* programme is believed to have a strong and potent health benefit for cardiac patients, and may eventually results in sustained effect on physical and mental health outcomes.

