## **4. General Considerations**

### **4.1 Timing of analyses**

The final analysis of primary objective will be performed when all subjects have completed T1 or dropped out prior to T1. Data should meet the cleaning and approving requirements and SAP should be finalised and approved.

The final analysis of other objectives will be performed when all subjects have completed T2 or dropped out prior to T2. Data should meet the cleaning and approving requirements.

The cleaning and approving requirements are

- all expected CRFs have been entered,
- all queries are resolved,
- all data are consistent,
- data is determined to be clean and
- the expected centre signatures have been applied

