#### **4.2.2 Per protocol analysis population**

The per protocol population consists of all subjects who adhere to the major criteria in the protocol and who have a cardiopulmonary exercise test (CPET) test with sufficient quality of tests at T0, T1 and T2. For the intervention group this implies subjects who complied with the use of the smartphone (use of the smartphone on at least 4 days per week with a minimum of 30 minutes of activity per day with a total registration of 150 minutes of activity per week during 21 weeks) during the first 6 months of the study.

Sufficient quality of CPET is defined as follows: identical protocol used in tests to be compared, respiratory exchange ratio (RER)  $\geq 1.1$  (or, if RER  $< 1$ , if delta between T0 and T1 and/or T2  $\leq 0.05$ ), and test duration  $\geq 4$  min (excluding warm-up), no signs of mask leakage or other equipment failure by visual inspection of CPET data.

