## **16. Conduct of statistical analysis**

All statistical calculations will be performed using SAS version 9.3 or higher, SPSS version 19 and R version 3.3.1., R Core Team (2016). Statistical analysis will be performed by the beneficiaries Bern, Santiago, Ludwigshafen, Copenhagen and CRO Diagram. Diagram will have an overview of all analyses that will be performed.

Diagram, as reviewing party, will independently reproduce the primary analyses and summary statistics table X, Y, Z. Diagram will explicitly check the code producing tables A, B & C (selected at random) as well as other pieces of code as desired. Each beneficiary is responsible for quality control of all macros and programs used during the analysis.

[figure not shown]

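### Protocol 7.5 unblinds the outcome assessor on an unexplained safety ground, although VO2peak can be read and test quality judged without knowing the arm

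*Combined protocol and SAP*

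**What the plan says.** Protocol 7.5 puts three roles under one rule with one reason: "The patient, care provider and outcome assessor will not be blinded to the intervention itself because of safety concerns". The concern is not specified.

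Protocol 10.3 says of the tests: "Non-invasive cardiac testing procedures in this study are not related to any potential risk for the participant". It adds that maximal ergometer tests are supervised in hospital. On home exercise, given instruction and telephone coaching, it says: "we expect no potential risk for them to exercise in their home environment".

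Under Protocol 7.6, VO2peak comes from a supervised incremental maximal cycling test, "using a continuous gas analyser", with one protocol for all tests and the modality held constant across visits. For patients who cannot do it, "this test will be replaced by a 6 Minutes Walking Test". SAP 5.1 brings a VO2peak approximated from that walk into the primary endpoint.

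The primary analysis uses the full analysis population, which is every randomised patient with consent (SAP 4.2.1). The CPET quality criteria appear only in the per-protocol definition (SAP 4.2.2) and must be met at T0, T1 and T2. They are an identical protocol, RER, test duration, and "no signs of mask leakage or other equipment failure by visual inspection of CPET data". SAP 4.3 wants each patient's status in both sets fixed before analysis starts.

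On timing, SAP 4.1 says: "The final analysis of primary objective will be performed when all subjects have completed T1 or dropped out prior to T1". The other objectives wait for T2. On analysts, SAP 16 says: "Statistical analysis will be performed by the beneficiaries Bern, Santiago, Ludwigshafen, Copenhagen and CRO Diagram". Neither document describes masked reading, masked quality assignment, or any limit on who sees T1 results by arm while T2 testing continues.

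**The concern.** The patient and the coach cannot be blinded to a smartphone programme. The assessor is a different case. An assessor can influence VO2peak in two ways: by how hard the patient is pushed during a maximal test, and by how the trace is read and its quality judged. The second needs no patient contact, so a safety reason cannot account for leaving it unmasked.

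The primary set has no effort criterion. Any systematic difference by arm in encouragement or reading therefore enters the primary difference unfiltered. The walk-test substitute has no gas measurement to anchor it.

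A second, smaller issue is order. Per-protocol membership includes a partly visual judgement on the T2 test. For late patients that judgement would be made after the primary result by arm exists, by people who are not said to be masked.

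**Working it through.** **Step 1: the safety reason against the rest of the protocol.** Protocol 7.5 cites safety for all three roles. Protocol 7.6 bases test safety on supervision, continuous ECG and heart rate, blood pressure at 3-minute intervals, and local guidelines. Protocol 10.3 attributes no potential risk to the testing. Nothing in these sections says why the arm must be known to run the T1 or T2 test, and reading an exported trace raises no safety question. The sections need reconciling.

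**Step 2: where an effort criterion applies.** RER and duration are in SAP 4.2.2 (per-protocol) and absent from SAP 4.2.1 (full analysis set). SAP 5.1 runs the primary analysis in the latter.

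**Step 3: the plan's own numbers (Protocol 5.4, SAP 3).** Inputs: difference 3.0; SDs 5 and 6, so σ = √[(25 + 36)/2] = 5.523; two-sided α 0.05; power 80%; ICC 0.05; withdrawal 30%.

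- Normal approximation: n = 2σ²(1.960 + 0.842)²/3.0² = 53.2, rounded up to 54. The t-based solution is 54.2, rounded up to 55, as stated.
- ICC step: 55 × [1 + (11 − 1) × 0.05] = 82.5, rounded up to 83, as stated. This takes 11 patients per cluster, which is 55 over five centres, although six are stated. This point does not turn on that.
- Withdrawal: 83/0.70 = 118.6, rounded up to 119, as stated.

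None of these figures changes with blinding.

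**Step 4: what a bias of a given size would do.** The documents give no bias, so b is assumed. With no true effect, SE = 5.523 × √(2/n) and P(reject) = P(|Z + b/SE| > 1.96). The result is the same whichever arm the bias favours.

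| Assumed b (ml/kg/min) | b/3.0 | 83 per arm (SE 0.857) | 55 per arm (SE 1.053) |
|---|---|---|---|
| 0.25 | 8% | 6.0% | 5.6% |
| 0.5 | 17% | 9.0% | 7.6% |
| 1.0 | 33% | 21.5% | 15.8% |
| 1.5 | 50% | 41.7% | 29.6% |

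The 83 column ignores clustering; the 55 column uses the size before ICC inflation. Neither allows for the baseline adjustment in the planned model.

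**Step 5: the order of T1 analysis and T2 testing.** Suppose even accrual over A months and L months from the last T1 visit to the T1 results. The share of patients with T2 still to come is (6 − L)/A. Neither A nor L is in the documents. SAP 4.1 requires entered forms, resolved queries, clean data and centre signatures first, so L is above zero.

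- A = 36, L = 2: 4/36 = 11%, about 26 of 238, or 0.70 × 26.4 ≈ 19 after the planned withdrawal.
- A = 18, L = 2: 4/18 = 22%, about 53 of 238, or 0.70 × 52.9 ≈ 37.
- L = 6 or more: none.

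For these patients SAP 4.3 cannot be met as written: per-protocol status depends on a T2 test that does not yet exist when the primary analysis starts.

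**The case against.** The best defence is that the endpoint is instrumented. Gas exchange is measured continuously, all tests follow one protocol, and the modality is fixed across visits. The primary analysis is also repeated in the per-protocol set, where RER and duration rules apply, and only mask leakage and equipment failure are judged by eye. All this is true and limits the bias. It does not remove it. The per-protocol repeat also selects intervention patients on smartphone compliance, so it is not a clean effort check, and SAP 18 calls it supportive only.

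It can also be said that nobody can call the safety reason inapplicable when it is unspecified. That stands, which is why the request is to state it and reconcile it with 10.3. Patients' own effort stays unblinded whatever is done.

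Several stronger readings are tempting but unsupported:

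- A reader might infer that the early T1 analysis biases the primary endpoint. It cannot, because every T1 test is over by then. Nor is there an alpha problem: this is the planned final primary analysis, not an interim look.
- A reader might infer that coaches run the tests, or that the analysing partners do. Protocol 7.4 names who may coach and SAP 16 names who analyses; neither document says who tests, or that results reach testers. The gap is a missing rule.
- A reader might infer that the bias favours mCR. Encouragement could differ either way, and a null T1 result would not push T2 towards mCR.
- A reader might take 6/36 to 6/18, or 17% to 33% of patients (about 40 to 79), as still awaiting T2 at the T1 analysis. That ignores the cleaning requirements in SAP 4.1.
- A reader might infer that event adjudication is unmasked. Protocol 8.3 leaves committee procedures to a separate document.

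**Conclusion.** The point holds in limited form. Protocol 7.5 unblinds the assessor without a reason that covers reading the data or judging test quality, on an effort-dependent endpoint whose primary analysis set has no effort criterion. The resulting bias is avoidable in part, and its size and direction are unknown. The Step 4 rates show only what an assumed bias would do.

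The T1 timing is a separate and lesser matter. It threatens T2 outcomes and per-protocol assignment only, and the number of patients affected rests on assumed accrual and cleaning times. T2 is still not peripheral, since the primary hypothesis (Protocol 3) and the SAP's primary objective (2.1) both include T2-T0. SAP 4.1 should be reconciled with that wording, because it analyses the primary objective at T1.

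The change is worth making because its main parts use data already collected and leave 119 per arm as it is.

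**What to change.** **Protocol 7.5.** Limit the unblinding to the patient and the care provider or coach. State the safety reason and reconcile it with 10.3. Add that VO2peak and walk-test values are read, and CPET quality is assigned, from exports with the arm removed. Where existing rosters allow, have the T1 and T2 tests run by someone who does not coach that patient. This last step is the only one that acts on encouragement during the test; masked reading acts on reading and quality alone. A strict requirement for separate testers is not proposed, because the documents do not describe centre staffing.

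**SAP.** Report peak RER by arm at T0, T1 and T2 in the full analysis set as an effort check. It will show an effort difference without saying whether tester or patient caused it, and it cannot cover walk-test patients. In 4.2.2 and 4.3, assign CPET quality and per-protocol status masked to arm. The smartphone criterion exists in one arm only and would reveal it, so add it by program from recorded use once the masked assignments are fixed. Say in 4.3 how status is set for patients whose T2 test is still to come.

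**Optional.** Restrict T1 results by arm to the analysts, and keep them from testing staff, until the last T2 test. SAP 4.1 and 16 must then be amended together, because several partners analyse and the CRO independently reproduces the primary analysis.

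**Cost.** Wording changes, one data-handling step to strip the arm from exports, and one table. If the option is taken, the centres see the T1 result later, by up to about 6 months.
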